## Methods

### Overview of study procedures

First, we will supplement the already-developed RIVER peer grief approach with materials needed to rigorously test its effectiveness (Aim 1). We will engage three advisory boards (family, research, and medical examiners) to (1) develop recruitment materials and procedures for recruiting grievers who interact with MEOs (2), adapt RIVER training materials to local MEO regions, and (3) develop fidelity measures. Next, we will conduct a pilot test of the RIVER peer grief support model with at least twenty people who are bereaved by a drug overdose death and recruited through MEOs. We will determine the feasibility and acceptability of griever engagement procedures, as well as grievers’ satisfaction with RIVER peer grief support (Aim 2).

In our third aim, we will use an RCT to test the effects of RIVER plus EUC compared to EUC alone for people who are bereaved by a drug overdose death and recruited from MEOs (Aim 3). People bereaved by a drug overdose death will be randomized to receive RIVER plus EUC or the EUC alone condition. RCT participants (*N* = 320 at baseline; 208 at 12-month follow-up) will be assessed on their experience of proximal and distal grief, substance use, and mental health outcomes at baseline, and during 3-, 6-, and 12-month-follow-ups. We will also conduct qualitative interviews with a subset of participants at the end of the study to contextualize the mechanisms in which the RIVER model affected them. Finally, we will collect qualitative and quantitative data from peer grief allies at the beginning and end of the RCT to explore how delivering peer grief support affects their well-being.

### Advisory boards

We will have three advisory boards that guide our research. The Family Advisory Board will consist of six family members who are bereaved by overdose, many of whom are leaders in community organizations that offer peer grief support. The goals of the FAB will be to give voice to the experiences of people who are bereaved by overdose and to provide strategic guidance on all aspects of the research. The Research Advisory Board will consist of nine members who have expertise within the fields of addiction and overdose bereavement. Their role will be to provide strategic guidance on the study design, appropriateness of the outcomes, analyses, and the interpretation of study results. Finally, the Medical Examiner Advisory Board will consist of seven members and their role will be to provide direction on data exchange and engagement workflows, and enhancement of scalability and sustainability planning of peer grief support in MEOs. We will meet quarterly with each advisory board throughout the study period.

### RIVER peer grief model

Grief work using the RIVER peer grief support model is dynamic and varies based on the individual’s specific circumstances, such as their relationship to the decedent (e.g., whether the relationship was strained) and the circumstances around the death (e.g., whether the death was anticipated). These factors can substantially impact grief and substance use outcomes in the bereaved [21]. At minimum, a RIVER peer grief ally will meet with a griever for at least three 45- to 75-minute virtual sessions. Meetings range in frequency from weekly to monthly (often less over time), and it is common for the meetings to continue for at least a year. These ranges are variable, depending on the wishes and agreement of the griever and the peer grief ally. Pilot data on the number and cadence of peer grief support sessions will be used to determine the minimum and maximum number of peer grief support sessions used in the RCT. In the pilot and RCT, peer grief allies will also provide grievers with the same materials that are part of the EUC, which include a psychoeducational booklet about grief [51] and a local mental health and grief support resource list.

#### Peer grief ally training and supervision

PSCP has a process for onboarding peer grief allies that assesses their readiness to deliver peer grief support given their own bereavement, their willingness to engage in ongoing supervision, their completion of at least 16 h of training, and the results of background checks. Background checks include identity verification and review of state and federal criminal records in accordance with institutional requirements. These checks identify active legal restrictions or unresolved charges that would prohibit participant-facing work. Past justice involvement is not automatically exclusionary; eligibility decisions consider relevance, recency, and potential risk to participant safety. The 16-hour training is broken into two parts. The first half of training focuses on using the RIVER peer grief support approach. Peers are trained in this process model through a combination of didactic information, discussion, and role plays. Peers are trained to identify clinical problems (e.g., posttraumatic stress disorder) and risks (e.g., dangerous substance use, suicidal crises) and taught how to connect people to clinical and emergency services as needed. The second part of the training addresses ways that delivering the RIVER peer grief support model could affect peers’ own well-being and grief process, both negatively through re-traumatization and positively through posttraumatic growth. Peers are informed about well-being resources available through PSCP and are encouraged to use these if they experience re-traumatization or other negative impacts of peer grief work. This portion of the training also includes discussion of regional demographic characteristics, paired with guidance on using a cultural humility approach when supporting participants. Peer allies are encouraged to ask open-ended questions and use reflective listening to understand what is important to each participant, rather than making assumptions based on regional or demographic information. RIVER supervisors meet individually with peers each week to coach them in their delivery of the RIVER peer grief support model and review documentation. As part of this study, supervisors will review and discuss audio recordings of sessions. Supervisors will also explore how grief support delivery impacts the peers’ well-being (e.g., identifying re-traumatization, risky substance use, etc.). Peers are advised to engage with a licensed clinician at PSCP if they experience re-traumatization and to attend monthly group reflective supervision in which they reflect with other peer grief allies on how their work affects their own grief journeys.

#### Enhanced usual care (EUC) for grief support

The EUC condition involves proactive outreach to supply grievers with existing, published psychoeducational booklet about grief and a list of grief support resources in their community in addition to what MEOs provide to grievers. We will provide participants a psychoeducational booklet about grief developed by an organization called *What’s Your Grief* [51]. This 12- page booklet was developed for a lay audience of people bereaved by any sort of death (i.e., not specifically a drug-related death) and has been used by PSCP in their general and overdose specific bereavement work [51]. We will distribute booklets in either English or Spanish, depending on the preference of the griever. We will also provide participants with a list of local grief, mental health, and substance use treatment resources.

### Setting

We will primarily conduct our study in regions that have the highest prevalence of overdose bereavement (i.e., New England and the central Southeast [11]). We will also conduct the study in the Pacific region, where the prevalence of overdose bereavement is lower compared to other US regions, to account for the possibility that grievers experience stigmatization, isolation, and a dearth of grief resources in communities where overdose bereavement is less common. We will partner with MEOs in the state of Connecticut; Jefferson County, AL; and San Diego County, CA. Despite differences in the prevalence of overdose bereavement in these communities, the number of overdose deaths in each region is high. Partnering with MEOs in these locations allows us to bolster bereavement support services in communities deeply impacted by drug overdose deaths.

### Aim 1 procedures

We will take a process-oriented [52] approach to optimizing the RIVER peer grief support model that PSCP has already created, while maximizing both internal and external validity as we prepare for rigorously evaluating the RIVER model’s effectiveness. First, we will refine RIVER training materials. We will work with local MEOs to customize training materials as informed by the local context (e.g., encouraging cultural humility, sharing local trends in next-of-kin demographics, describing how drug use has affected their local community, how to address grievers who use substances themselves). Second, we will develop measures of fidelity and adherence to the RIVER peer grief support model. Like motivational interviewing [53], RIVER is a process model that describes the style in which an intervention is given. Thus, we will develop a RIVER fidelity assessment and coding manual similar to the Motivational Interviewing Treatment Integrity (MITI) measure [54] whereby coders rate peer grief facilitator speech on each of the RIVER domains (relate, invite, validate, empower, reassure) using a 5-point Likert scale. Finally, we will work with our MEO partners to develop recruitment workflows and establish data sharing plans to support proactive outreach to people bereaved by overdose by our research data collection staff.

### Aim 2 procedures

We will work with our three partnering MEOs to recruit 20 people bereaved by overdose for a pilot study of the RIVER peer grief support model (see Fig. 1). We will recruit one bereaved adult per decedent to participate in study assessments but, in keeping with PSCP’s inclusive practice, we will deliver the RIVER peer grief support model to other grievers who lost the same decedent upon request. We will offer study participation to the bereaved adult who the MEO obtains consent-to-contact, but remain flexible if that person feels another adult who is not the designated NOK would be a better fit for the study (e.g., someone who may benefit more from peer grief support). Participants will be people who (1) lost a loved one to an unintentional drug overdose death within the past year (2), are age 18 and older (3), fluently understand English or Spanish, and (4) have the capacity to give consent (e.g., excluding those with severe cognitive impairment, those in active psychosis, and those with developmental disabilities). Based on early feedback from our Medical Examiners Advisory Board, we will operationalize drug overdose deaths as those caused by intoxication from illicit substances (e.g., heroin), prescription substance misuse (e.g., using opioids in a way that was not prescribed), and/or counterfeit pills. Deaths in which intoxication exacerbated underlying medical conditions will be considered drug overdose deaths. Deaths that result from an adverse reaction to prescription medications that were used as prescribed (e.g., allergic reaction) will not be considered drug overdose deaths.

The study will exclude people who (1) need hospitalization for psychiatric symptoms or substance use disorders (2), have active suicidal ideation (3), lost someone to a drug overdose death more than one year ago, or (4) lost someone to a drug overdose death that was suicidal in nature or of undetermined intent. Those who use substances but do not require hospitalization for substance use disorder will *not* be excluded given the connection between substance use and poor grief outcomes. We will include only those grieving death that occurred within the past year because prolonged grief disorder can be diagnosed no earlier than 12-months after a loss [55] and we aim to evaluate the effectiveness of the RIVER peer grief support model in preventing this outcome. On the recommendation of our advisory boards, we will exclude people bereaved by suicide and deaths of undetermined intent because the bereavement experiences of these populations differ from those bereaved by unintentional drug overdose deaths.

We will proactively recruit people bereaved by overdose from MEOs. MEOs routinely identify and contact the legal next-of-kin to overdose decedents in order to provide them with death notifications. At the participating MEOs, nearly all manner and cause of death rulings are complete within 60 days of receiving the decedents’ remains. After this determination, staff at our partnering MEOs will ask families bereaved by overdose to give consent to be contacted by the study team. MEO or study staff will provide grievers with a postcard that describes the study, provides a QR code that links grievers with a page with additional study details and a brief animation video describing the study (see Fig. 2). Study engagement procedures will be carried out by MEO staff including medical examiners, death investigators, and chaplains.

**Fig. 2 Fig2:**
[figure not shown]
Pilot and RCT study design

Next, the study team will engage potentially eligible grievers. We will contact grievers to describe the study, screen them for eligibility, conduct the informed consent process, gather baseline data, and send the psychoeducational materials and list of local grief resources that make up EUC. The study team will contact families 30 to 90 days after they receive the death notification to contact grievers. This delay in outreach was recommended by PSCP and our advisory boards who suggested that grievers may be focused on making funeral arrangements and addressing immediate stabilization needs in the immediate aftermath of loss. However, grievers who contact the study team earlier may be enrolled earlier upon their request.

Enrolled participants will be referred to PSCP for peer grief support. PSCP will review grievers’ information and match them with a peer grief ally. Grievers are matched to an ally when possible, based on relationship to the descendent (e.g., parent vs. spouse) and geographical location (e.g., time zone). PSCP will contact the participant within three business days to schedule the first RIVER peer grief support session. During the first session, RIVER peer grief allies will schedule at least two additional sessions over the initial three months after enrollment at a cadence agreed-upon the peers and participants. All sessions will be conducted virtually or by phone. Sessions will be audio recorded to support peer grief ally supervision and fidelity assessment.

Three months after baseline, the study team will conduct 45-minute interviews with the participant. Participants will complete the Feasibility Intervention Measure (FIM) [56] that tests whether an intervention can be successfully used or carried out within a given setting. The FIM includes questions about how workable, possible, doable, and easy the RIVER peer grief support model was for the participant. Acceptability will be evaluated using the Acceptability of Intervention Measure [56] that tests how agreeable, palatable, or satisfactory the intervention was. Finally, we will use the Client Satisfaction Questionnaire (CSQ) [57, 58] where scores of at least 26 of 32 (81%) indicate acceptability of an intervention [59]. Questions include whether the intervention was a quality service, met their needs, and helped them cope. Participants will be asked open-ended questions about their experience with recruitment (e.g., “What did you like or not like about that process?”) and peer grief support (e.g., “What did you think of your discussions with your peer grief ally? How can we make the discussions helpful to people from different backgrounds?”). Interviews will be recorded and transcribed. Participants will be compensated $50 at baseline and $75 at the follow-up interview.

#### Aim 2 analyses

We will quantitatively analyze engagement, feasibility, acceptability, and satisfaction using summary statistics such as rates or means, as appropriate. Secondary analyses will explore differences in grief-related outcomes by number of peer grief sessions received by grievers; we will use linear regression to determine whether higher numbers of peer grief sessions are associated with better PGD and PGD-related outcomes. These analyses will help us to inform the minimum number of peer grief support sessions that will be used in this next phase.

Qualitative interviews will be coded by two coders to identify common themes using content analysis in Dedoose. We will also conduct a rapid content analysis [60] to efficiently glean insights that can be incorporated while still recruiting for the study. These methods include having a first coder writing detailed notes during each interview and categorizing across comments about the feasibility and acceptability of recruitment as well as the RIVER peer grief support model. Then, a second coder verifies the codes after listening to the interview recording. Analysts will meet regularly to discuss any differences and align on ratings. Coding will be iterative and will include comments that may be positive, negative, or neutral. Classic content analysis will be used to categorize quotes within each concept into themes (e.g., proactive outreach from the MEO was helpful) [61]. We chose a sample size of 20, however sample size will ultimately be determined by thematic saturation in qualitative analyses, at which point data collection becomes redundant [62]. If needed to form consensus themes, we will recruit additional participants for the pilot. We will follow procedures to maintain rigor of qualitative analyses, including an audit trail and data triangulation following the Standards for Reporting Qualitative Research (2014) [63] for data collection and analysis.

### Aim 3 procedures

We will recruit people who are bereaved by overdose from our three partnering MEOs for an RCT comparing the RIVER peer grief model plus EUC to EUC alone. Participants will complete assessments at baseline and 3-, 6-, and 12-month follow up. The inclusion and exclusion criteria for the RCT will be identical to Aim 2 unless advised otherwise by the advisory boards. We aim to recruit 320 people with a goal of 65% retention (208 people) at the 12-month follow-up.

We will also recruit the RIVER peer grief allies (up to 10) to complete a baseline and follow-up survey prior to and after the RCT. They will also be invited for a brief qualitative interview post-RCT to assess their experiences delivering peer grief support.

#### Randomization and stratification

Upon completion of the baseline survey, participants will be randomly assigned to the RIVER peer grief support model plus EUC or to EUC alone. Randomization will involve a stratified permuted block randomization with random size blocks. This ensures the number of people allocated to each group is approximately equal throughout recruitment [64]. We will stratify the sample by history of opioid misuse (lifetime heroin use and/or lifetime prescription opioid misuse) [65], under the premise that (1) drug overdose bereavement among PWUD may increase risk for future drug overdose deaths which typically involve opioids and (2) PWUD may experience grief problems that are more severe or different from people bereaved by a drug overdose death who do not use drugs. Randomization will be performed within each stratum.

#### Measures

All measures will be collected using surveys administered by an interviewer over the phone. We have selected measures that are reliable and valid in populations experiencing grief, as well as measures from the NIH HEAL Initiative Common Data Elements Repository and the NIH PhenX Toolkit [66] (see Table 1). Our primary outcome is PGD, and the associated outcomes that we are evaluating have previously demonstrated a relationship with the severity of grief symptoms experienced. We also have additional proximal and distal outcomes that will serve as pre-specified secondary outcomes (see Table 1; Fig. 3). Other potential covariates include participants’ relationship to the decedent, time since the death, history of exposure to other drug overdose deaths (i.e., number of people they knew who died by overdose), drug of choice (for PWUD enrolled in the RCT), and service utilization (measured using the NIH PhenX Access to Health Services Protocol derived from the National Health Interview Survey [67]).

**Table 1 Tab1:** Outcomes

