## Study aims

The current study has three aims. In aim one, we will adapt training materials for the RIVER peer grief support model to fit the needs of the communities surrounding our partnering MEOs, develop a fidelity measure, and create workflows for engaging grievers and connecting them with peer grief allies. In aim two, we will conduct a pilot test to evaluate the acceptability and feasibility of engaging grievers via MEOs, refine the fidelity measure, and evaluate if peer grief support using the RIVER model was satisfactory to grievers. In aim three, we will conduct a randomized controlled trial (RCT) to evaluate the effectiveness of the RIVER peer grief approach plus enhanced usual care (RIVER + EUC) to prevent PGD and substance misuse in people bereaved by overdose, over and above any effects of EUC. Participants will be recruited from MEOs and will complete baseline, 3, 6, and 12-month surveys on (a) proximal outcomes (i.e., connectedness, acceptance, and coping) and (b) long-term outcomes (i.e., PGD and substance misuse). Post-RCT qualitative interviews of study participants and mixed methods assessments with peer grief allies will supplement data collection and allow us to understand the characteristics of the RIVER peer grief approach that drive effectiveness and its impact on peer grief allies.

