**Distal & Proximal Outcomes (Aim 3)**		
Grief Symptoms (Primary)	Presence and extent of persistent emotional, cognitive, and behavioral responses to the loss by the griever (e.g., intense yearning, preoccupation with the deceased, difficulty accepting the death, and disruptions in daily functioning)	Brief Grief Questionnaire (BGQ)
Connectedness	Extent to which individual still feels bonded to their deceased loved one and the people in their community	Continuing Bonds Scale Multidimensional Scale of Perceived Social Support\
Grief Acceptance	Presence and extent of adaptive beliefs that support the griever in acknowledging the loss, tolerating painful emotions, maintaining a meaningful connection with the deceased, and re-engaging in their daily life	Typical Beliefs Questionnaire
Coping Strategies	Cognitive, behavioral, social, and spiritual tools the griever uses to manage the emotional, practical, and existential challenges that arise after a loss	The Coping Assessment for Bereavement and Loss Experiences (CABLE)
Grief-related Avoidance	Presence and extent of efforts used by the griever to evade external and internal reminders of the loss (e.g., certain places, activities, thoughts, or emotions about the deceased) and reduce distress	Grief-Related Avoidance Questionnaire (GRAQ)

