### Data management and analysis plan

Aim 3 will test the effect of receiving the RIVER peer grief support model plus EUC compared to EUC alone by contrasting outcomes of grief and using regression-based modeling to leverage all time points while adjusting for the stratification variable. We will use Intent-to-Treat analyses. Hypotheses regarding the effectiveness of the RIVER peer grief support approach will be tested with a repeated measures mixed-effects linear model, with experimental group, time (4 assessment time points), and their interaction as fixed effects. Inclusion of the interaction term will allow for examination of the difference in response trajectories between intervention arms. We will also include the stratification variable as a covariate in the model. For missing data, we will proceed with likelihood-based mixed-effects models, which are valid under the Missing at Random (MAR) assumption. For non-ignorable missingness, we will add sensitivity analyses. Qualitative interview data with peer grief allies will also be used to contextualize quantitative results. For example, if allies share that support was more or less challenging for certain groups, we may explore potential moderators of the treatment effect.

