### Power

We powered our trial to detect a moderate effect size based on arm-differences of proportions of prolonged grief, due to the dearth of pilot data on mean differences. We considered an 18% arm difference in rates of prolonged grief symptoms, assuming 27% in the RIVER plus EUC arm and 45% in the EUC only arm. Since the RIVER peer grief support model has not yet been evaluated in those specifically bereaved by drug overdose deaths, we conservatively used estimates of proportions reported on rates of PGD among those bereaved by suicide [6]. We will have 80% power to detect a moderate effect size of a Cohen’s d of 0.4. We based this calculation on a two-tailed test of proportions for the null hypothesis of no difference in arms, and a significance level of 0.05. We are also adequately powered to perform repeated measures analysis to detect a group by time interaction term in a mixed model to address Aim 3. With our proposed follow-up sample size (*n* = 208), we have 90% power to detect a group by time interaction, expecting a Cohen’s d of 0.4 as before, and assuming adjustment of the baseline grief score, and a correlation of 50% between repeated measures.

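### The aim and Measures text make prolonged grief disorder the primary outcome, but Table 1 and the linear model use a symptom score, so prevention of the disorder is not directly tested

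*Protocol article*

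**What the plan says.** All references are to the protocol article.

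- **Study aims** gives the purpose of the randomised trial as "to prevent PGD and substance misuse in people bereaved by overdose".
- **Measures** states "Our primary outcome is PGD".
- **Table 1**, in the block of distal and proximal outcomes for Aim 3, marks one row "Grief Symptoms (Primary". Its instrument is the BGQ, and it covers both presence and extent of grief responses.
- **Data management and analysis plan** tests the effectiveness hypotheses with a "repeated measures mixed-effects linear model, with experimental group, time (4 assessment time points), and their interaction as fixed effects". It describes no binary analysis.
- **Aim 2 procedures**, whose eligibility criteria carry over to the trial unless the advisory boards advise otherwise, says "prolonged grief disorder can be diagnosed no earlier than 12-months after a loss". It places study outreach 30 to 90 days after the death notification.
- **Power** gives two calculations. The first rests on proportions with prolonged grief (27% against 45%), chosen "due to the dearth of pilot data on mean differences". The second is for the group-by-time term of the mixed model, with 208 followed up, d = 0.4, adjustment for baseline grief score and a correlation of 0.5.

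**The concern.** A disorder that is present or absent and a mean symptom score are different outcomes. The first calls for a risk or a proportion at a time when the diagnosis is possible. The second calls for a difference in means. The aim and the Measures text claim the first, while Table 1 and the model deliver the second.

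What is at stake is the conclusion the trial may draw. If the plan is followed and the result is favourable, the finding is that mean BGQ scores followed a better course with RIVER. Read against the stated aim and primary outcome, that would be reported as prevention of PGD, which the analysis does not estimate.

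**Working it through.** **1. Can PGD be the response in the four-time-point model?**

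Inputs: no diagnosis before 12 months after the loss; loss within the past year at entry; outreach 30 to 90 days after notification (all Aim 2 procedures); assessments at baseline, 3, 6 and 12 months (Aim 3 procedures). Assumptions: the trial uses the pilot's outreach timing, notification comes soon after the death, and enrolment follows outreach promptly. Thirty to 90 days is taken as about 1 to 3 months.

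| Assessment | Months since loss | PGD diagnosable? |
|---|---|---|
| Baseline | about 1 to 3 | no |
| 3 months | about 4 to 6 | no |
| 6 months | about 7 to 9 | no |
| 12 months | about 13 to 15 | yes |

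This describes most participants, not all. Someone enrolled 9 months or more after the loss would reach month 12 by the 3-month visit. The baseline row needs less: eligibility requires a loss within the past year, so baseline precedes the point of diagnosis for essentially everyone. A linear model with all four time points can therefore only have a symptom score as its response. The Power section agrees, since it adjusts for a baseline grief score.

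**2. Is the modelled score powered?**

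The stated figure is 90% with 208 followed up (104 per arm), d = 0.4 and r = 0.5, two-sided 0.05. Treating it as a baseline-adjusted contrast of two means:

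- Residual SD = √(1 − 0.5²) = 0.866
- z = (0.4 / 0.866) × √(104/2) − 1.96 = 3.331 − 1.96 = 1.371
- Power = 91.5%

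The stated 90% is supported.

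**3. Is the calculation on proportions right?**

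The stated figure is 80% for 27% against 45%, two-sided 0.05. That sentence gives no sample size, so 104 per arm is assumed from the 208 completers.

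- Pooled proportion = 0.36
- SE under the null = √(2 × 0.36 × 0.64 / 104) = 0.0666
- SE under the alternative = √((0.27 × 0.73 + 0.45 × 0.55) / 104) = 0.0654
- z = (0.18 − 1.96 × 0.0666) / 0.0654 = 0.76
- Power = 77.6%

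The arcsine version gives 77.8%, a continuity correction 72.9% and Fisher's exact test 73.5%. With all 320 enrolled (160 per arm) the figure would be 92.2%. For 80%, the pooled formula needs 111 per arm: 222 completers, or 222 / 0.65 = 342 enrolled.

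**4. Where does the gap between the two power figures come from?**

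Cohen's h for 45% against 27% is 2·asin(√0.45) − 2·asin(√0.27) = 0.378, which the article rounds to 0.4. At 104 per arm without adjustment, 0.378 gives 77.8%. An effect of 0.4 gives 0.4 × √52 − 1.96 = 0.924, or 82.2%, whether it is read as h or as d. Baseline adjustment then raises 82.2% to 91.5%. The gap comes from rounding plus adjustment.

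**The case against.** The best defence is that Measures names the construct and Table 1 names its instrument. Only one row is marked primary, no rival instrument competes with it, and the model fits that row. On this reading the article should simply have written PGD symptoms. That explains how the wording arose, but it leaves the aim of preventing a disorder resting on a contrast of scores.

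Several stronger readings are tempting, and the article does not support them:

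- **That the proportion with prolonged grief is a third primary outcome, or that the analysed outcome is unpowered.** The Power section says openly that proportions stand in for missing data on means, and it powers the mixed model separately.
- **That the power depends on whether the outcome is binary or continuous.** Step 4 of the working shows otherwise.
- **That the investigators keep a choice between binary and continuous results once data are seen.** The analysis section commits the effectiveness hypotheses to the linear mixed model and offers no binary alternative.
- **That naming substance misuse in the aim contradicts its secondary status.** An aim may cover primary and secondary outcomes.
- **That the lack of a BGQ cut-off is itself a fault.** An article commonly leaves such detail to the full protocol or analysis plan, which are not shown.

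**Conclusion.** The point holds as a mismatch between what is claimed and what is analysed. The aim and Measures name PGD, Table 1 and the model concern a symptom score, and the article's own diagnostic time limit rules out PGD as the response across four time points.

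A reader might go further and say the trial can tell us nothing about PGD. That is too strong. A lower mean score would be indirect support for prevention; it is just not a direct test of it.

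The consequence lies in the conclusion the trial may draw, not in the adequacy of the sample for the score, where the stated 90% checks at 91.5%. The calculation on proportions falls a little over 2 points short (77.6% against 80%), provided it refers to the 208 completers. That is a side finding, and the main point does not depend on it. The timing argument rests on the usual outreach schedule applying to the trial. For baseline it rests only on the eligibility limit of one year.

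**What to change.** - **Study aims, Measures and Table 1:** state the BGQ score as the single primary outcome, in the same words each time. Word the primary aim, and later the conclusion, as reducing grief symptoms.
- **Data management and analysis plan:** keep the group-by-time mixed model and name the primary contrast, for example the difference between arms at 12 months.
- **Secondary outcomes:** add prolonged grief yes/no, assessed at least 12 months after the loss, with a binary analysis. The 12-month visit meets that condition for participants seen on schedule. The rule that classifies a participant can sit in the full protocol or analysis plan.
- **Power:** present the mixed-model calculation (208 followed up, d = 0.4, r = 0.5) as the basis for the primary outcome. Show 27% against 45% as supporting only, with about 78% power at 104 per arm, or state the sample size to which the 80% refers.

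The cost is wording in five places, one extra analysis and a more modest claim. No change in sample size is needed.

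If the sponsor prefers to keep PGD as primary, it must be defined at a time at least 12 months after the loss, with a binary model and a matching sample size. On the article's own rates and retention, that means about 342 enrolled rather than 320.
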